### RCT Study Design

The ACCT2 study is a 1-year pragmatic randomized controlled parallel group open-label effectiveness trial including 96 Arabic-, Turkish-, or Urdu-speaking individuals with T2D (Figure 2). The intervention consists of 6 visits to SDCC. All visits are based on specific values and competencies of HCPs, which are important in the organization, implementation, and completion of the intervention.

**Figure 2 figure2:**

Visit flow.

### Values of the Intervention

The intervention is based on a person-centered approach [34,35]. A person-centered approach is characterized as a collaborative process between the participant and the HCP, wherein the participant’s priorities, preferences, and needs are incorporated into decisions regarding their diabetes treatment. It focuses on understanding the patient’s capacity and pace for change [34,35], where cultural competence among HCPs is crucial. This includes adapting attitudes to individual needs and recognizing the implications of emotional, cultural, social, and psychological consequences [17]. Striking a balance, HCPs must acknowledge potential cultural differences without letting them dominate encounters. The intervention’s visits consider individual circumstances, resources, expectations, and prerequisites for changes. In addition, it aligns with the empowerment treatment philosophy, where well-informed participants actively engage in diabetes management. The HCP’s role is to support the participant in making decisions, achieving goals, and overcoming obstacles [36].

### Study Visits

The visits will be run by the same diabetes nurse and endocrinologist under the responsibility of the investigator. Visits with dieticians will be arranged if requested by participants (up to 60 min per visit). For logistical reasons, windows are allowed for the visits (±30 days). The intervention staff includes the same diabetes nurse and endocrinologist, each overseeing the 48 participants in the intervention group. The 48 control participants will continue their care with their usual HCPs. A detailed visit flow is presented in Figure 2.

#### Visit 1

The first visit, lasting 60 minutes, will involve meeting with a diabetes nurse. During this visit, the focus will be on introducing the participant to the course of treatment and to a continuous glucose monitor (CGM; FreeStyle Libre 2 sensor), which the participant will use for the following 2 weeks. This will enable the participant to gain insight into personal glucose levels. In addition, the nurse will provide information about T2D and its treatment and discuss everyday challenges and topics relevant to the participant.

#### Visit 2

The second visit, lasting 60 minutes, will involve the same diabetes nurse. The main aim is to talk about pattern identification obtained from the CGM sensor for the past 2 weeks to enhance knowledge of lifestyle factors contributing to stable or fluctuating glucose levels. The nurse will engage in a dialogue about the challenges participants face in everyday life. A new sensor will be applied to the participant for the upcoming 2-week period.

#### Visit 3

During the third visit, lasting 45 minutes, the participant will meet with an endocrinologist. Patterns derived from the CGM sensor will be discussed to enhance participants’ comprehension of unique glucose levels and determine if any changes or solutions discussed during the second visit have been implemented and proven effective in promoting more stable glucose levels. The endocrinologist will evaluate patterns of variation, for example, focus on hypoglycemia, and make necessary adjustments in pharmacological treatment. The treatment plan will be negotiated with the participant, providing information on the rationale for the change in treatment regimen and potential benefits and risks. The participant will also be guided to continue self-monitoring of blood glucose according to individual plans.

#### Visit 4

During the fourth visit (2x30 mins), the participant will meet with the same endocrinologist and diabetes nurse. The main purpose is to evaluate and follow up on the participant’s everyday life with diabetes, medication use, and individual needs. The aim is to support the participant’s positive experience with the treatment and lifestyle changes, address misperceptions, and reinforce the information provided. If necessary, the endocrinologist will adjust the medication regimen.

#### Visit 5

During the fifth visit, lasting 30 minutes, the participant will meet with the same endocrinologist. The main purpose is to evaluate and follow up on the participant’s medication usage and individual needs. The aim is again to support the participant’s positive experience with the treatment and lifestyle changes, address misperceptions, and reinforce the information provided. If necessary, the endocrinologist will adjust the medication regimen.

#### Visit 6

During the sixth visit (20+30 min), the participant will again meet the same endocrinologist and diabetes nurse. The primary aim is to provide a comprehensive overview of the treatment progress and patterns obtained from the CGM sensor for the past 2 weeks. The participant will be instructed to apply the sensor at home 2 weeks before the last visit. If the participant prefers, they can be booked for a short visit at SDCC with the diabetes nurse to apply the sensor. The last visit will serve as an opportunity to ask any questions, clarify doubts, or express any specific needs the participants may have.

Besides the 6 visits, the participant will receive links to 4 short videos about T2D developed by the Danish Diabetes Knowledge Center at SDCC. The videos are translated into Urdu, Arabic, or Turkish and include knowledge on (1) T2D, (2) complications associated with T2D, (3) exercise and diabetes, and (4) carbohydrates and diabetes (for details on content, refer to [37]). Participants in the intervention group may also have visits, for example with a psychologist and a podiatrist, as part of their usual course of treatment.

To minimize the risk of intervention contamination, HCPs in the study will not interact with participants in the control group. The control group does not have access to any materials, technology, or other components provided to the intervention group. This will ensure that the 2 groups remain distinct, preventing cross-contamination and preserving the integrity of the intervention’s evaluation.

### Control Group

Participants in the control group will follow the standard course of treatment, which includes regular visits with a physician, often an endocrinologist, and a nurse at the T2D outpatient clinic at SDCC 3-4 times per year (Figure 3). These visits can be in-person or computer-based, depending on the preferences of the participant and HCPs. The standard course of treatment also often includes visits with a podiatrist and eye screening, and it may also include visits with a dietician and psychologist.

**Figure 3 figure3:**

Standard course of treatment over 1 year.

### Outcomes

#### Primary Outcome

The primary outcome is changes in HbA_1c_ (mmol/mol) from baseline to the end of the 1-year intervention.

#### Secondary Outcomes

The secondary exploratory outcomes encompass a range of metabolic and behavioral factors that may be linked to the intervention. These involve changes from baseline to the end of the intervention (1 year), including plasma lipids, markers of kidney function, hormones involved in glucose metabolism, blood pressure, resting heart rate, CGM (time-in-range, time-above-range, and time-below-range), body weight, and use of diabetes medication (Table 1).

**Table 1 table1:** Data collection.

Visit sequence number			Visit 1		Visit 2		Visit 3		Visit 4		Visit 5		Visit 6
**Clinical assessments**													
	HbA_1c_^a^	✓						✓		✓		✓	
	Plasma lipids	✓										✓	
	Blood pressure and resting heart rate	✓				✓		✓		✓		✓	
	Hormones involved in glucose metabolism	✓										✓	
	CGM^b^			✓		✓						✓	
	Markers of kidney function	✓										✓	
	Albumin-creatinine ratio	✓										✓	
	Body weight	✓										✓	
	Use of diabetes medication	✓										✓	
**Questionnaires**													
	Sociodemographic characteristics	✓											
	Diabetes distress (PAID-5^c^ scale) [38]	✓										✓	
	Well-being (WHO-5^d^) [39]	✓										✓	
	HLQ^e^ (3 items) [40]	✓										✓	
	Diabetes management (PRO^f^ scheme diabetes) [41]	✓										✓	
	MARS-5^g^ [42]	✓										✓	
	Acceptability, retention, and satisfaction [43]											✓	
**Interviews**													
	Individual interviews (subgroup of participants)							✓				✓	
	Interviews with HCPs^h^ delivering the intervention							✓				✓	

^a^HbA_1c_: hemoglobin A_1c_.

^b^CGM: continuous glucose monitoring.

^c^PAID-5: Problem Areas in Diabetes Scale–5.

^d^WHO-5: World Health Organization–Five Well-Being Index.

^e^HLQ: Health Literacy Questionnaire.

^f^PRO: patient-reported outcome.

^g^MARS: Medication Adherence Rating Scale.

^h^HCP: health care professional.

### Clinical Assessments

#### Blood Samples

Blood samples are, as part of the regular treatment protocol at the outpatient clinic in SDCC, routinely taken before visits. The participant must arrive at the SDCC laboratory at least 70 minutes before visit 1 and visit 6 for nonfasting blood sampling from the antecubital vein and urine analysis.

#### CGM Use

CGM is initiated using the authorized FreeStyle Libre 2 device. Participants will be provided with detailed information about the device during visit 1. It will be applied for 2 weeks. The monitoring will be repeated at visit 2 and again 2 weeks before visit 6. FreeStyle Libre 2 allows individuals to monitor glucose levels without routine fingerstick blood glucose testing. It is a small sensor worn on the skin that measures glucose levels in the interstitial fluid to display real-time glucose readings. With features such as trend arrows and built-in memory for data storage, FreeStyle Libre 2 supports diabetes management and provides insights into glucose patterns to inform decisions about medication, diet, and lifestyle.

#### Blood Pressure and Resting Heart Rate

Blood pressure and resting heart rate are measured using approved and calibrated equipment (Microlife BP A3 Plus) and taken with the participant after a minimum of 10 minutes of rest, without talking during the measurement. Measurements are repeated 3 times, separated by 2-minute breaks to prevent artificially elevated blood pressure resulting from an unfamiliar and potentially stressful environment. The mean value is calculated.

#### Height and Body Weight

Height is measured with the participant’s heels, buttocks, and upper back remaining in contact with the wall. Results are noted to the nearest 0.1 cm. Body weight is measured to the nearest 0.1 kg, with the participant wearing indoor clothes and no shoes.

#### Questionnaires

Participants will fill in a baseline questionnaire and a questionnaire at the end of the intervention (refer to Table 1). Questionnaires will be answered during the 70-minute waiting time between blood samples before visit 1 and visit 6. A project worker will be present to address technical questions. Questionnaires are translated into Urdu, Arabic, or Turkish following international standards [30]. The following measures will be assessed at baseline alone: marital status, cohabitation status, social network, educational level, and occupation. Participants’ acceptance of the intervention is only explored in the questionnaire at the end of the intervention.

#### Interviews

Interviews will be conducted by a qualitative researcher with a subgroup of participants in the intervention group after the last visit. Participants’ experiences during the intervention will be explored to examine experiences with the 1-year intervention, possible improvements, and important factors for successful implementation into the clinical setting. HCPs delivering the intervention will also be interviewed about acceptability and experiences with intervention delivery in the clinical context.

#### Measurement of Adherence

Adherence to the intervention is determined by calculating the number or percentage of visits during the intervention in which participants actively engage in all 6 scheduled visits. Per protocol is defined as ≥80% adherence.

### Statistical Considerations

#### Sample Size Calculation

A 5.0-mmol/mol change is the minimal difference for the primary outcome, HbA_1c_. This resulted in the total number of participants required to enter and complete this 2-arm, parallel-design trial of 88 participants. The sample size was estimated using a general linear model equivalent to a repeated measures mixed model with 2 time points (PROC GLMPOWER, SAS 9.4; SAS Institute). The estimation was based on the following conditions: an allocation ratio of 1:1, **α**=.05, **β**=.1, a mean HbA_1c_ level of 70 (SD 14) mmol/mol at each timepoint [44,45], and a correlation between repeated measures of 0.8 [46]. The total number of participants was multiplied by 1.1 to account for potential uncertainties in the conditions used in the power calculation and to account for potential dropouts, resulting in 96 participants.

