**Results:**

A 5.0-mmol/mol change in HbA_1c_ is the minimally important difference, requiring 88 participants. To allow for uncertainties and dropouts, the total was increased to 96. As of January 2025, a total of 88 participants have been recruited. Recruitment was completed in March 2025. Data collection will continue until December 2025, with the first results expected by March 2026.

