### Hypotheses

We hypothesize that a 1-year, person-centered and culturally sensitive intervention added to standard care will be superior for reducing HbA_1c_ in Arabic-, Turkish-, or Urdu-speaking individuals with T2D. Superiority will be claimed if the baseline-corrected difference between the 2 groups is equal to or surpasses the minimal important difference (5 mmol/mol) in favor of the intervention group and if the *P*<.05.

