#### Statistical Analysis

An intention-to-treat analysis, encompassing all randomized participants, will be conducted upon completion of the last participant’s final visit. A per-protocol analysis will be carried out, including participants who demonstrate compliance throughout the intervention. Data will be presented using standard descriptive statistics, with means and SDs for normally distributed data and medians with IQRs for data not conforming to normal distribution. Changes from baseline and distinctions in delta values between groups will be assessed using linear mixed-effects models, considering the outcome as a function of group, time, and the interaction between group and time, and accounting for a participant-specific random intercept. The adequacy of assumptions regarding normality and homogeneity of variances will be verified through graphical methods, and data will be log-transformed for analysis and subsequently back-transformed for presentation. In cases where model assumptions are not met even after logarithmic transformation, nonparametric statistical tests will be used. Statistically significant findings will be determined with *P*<.05 (2-tailed). To assess the potential impact of missing data on the primary outcome, a sensitivity analysis will be conducted, involving multiple imputations with missing data at follow-up, which will be included in the imputation process with the control group. Results will be presented as estimated mean changes, accompanied by 95% CIs, degrees of freedom, and, if appropriate, the test value.

Covariables such as age, sex, diabetes duration, and so on, will be included in analyses to assess their potential influence on the outcomes. This approach will allow us to adjust for confounding factors and provide an accurate estimation of the intervention's impact. In addition, if the intervention proves effective, a health economic evaluation will be conducted to estimate the cost per person. This evaluation will consider direct costs, for example, staff time and technology, alongside potential cost savings from improved health outcomes, reduced complications, and fewer health care visits.

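### The stated inputs need about 134 completers for 90% power, not 88; at those inputs, power is about 75% with 88 completers and 78% with 96

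*Protocol article*

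**What the plan says.** The Sample Size Calculation section of the protocol article gives a complete set of inputs:

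- Target: "A 5.0-mmol/mol change is the minimal difference for the primary outcome", HbA1c. The Hypotheses section makes clear that this is a baseline-corrected difference between the two groups.
- Error rates and allocation: "an allocation ratio of 1:1, α=.05, β=.1".
- Variability: "a mean HbA_1c_ level of 70 (SD 14) mmol/mol at each timepoint".
- Correlation: "a correlation between repeated measures of 0.8".
- Model: a general linear model described as equivalent to a two-time-point repeated-measures mixed model, run in SAS PROC GLMPOWER.

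The conclusion is: "This resulted in the total number of participants required to enter and complete this 2-arm, parallel-design trial of 88 participants". The total is then multiplied by 1.1, for uncertainty in the inputs and for dropout, to reach 96. The abstract repeats the result: "A 5.0-mmol/mol change in HbA_1c_ is the minimally important difference, requiring 88 participants".

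The Statistical Analysis section fixes two-tailed testing at .05. It plans a mixed model with group, time, their interaction and a participant random intercept.

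**The concern.** The article prints both the inputs and the answer, so the calculation can be repeated without outside information, and the two disagree by about a third.

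This matters because 90% power for the smallest difference held to be important is the main design claim for the primary outcome. A reader who believes it will take a non-significant result as fairly strong evidence against a 5 mmol/mol effect. If the real chance of missing such an effect is one in four or five rather than one in ten, that reading is not justified. The Discussion also lists the power calculation among the trial's methodological strengths.

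**Working it through.** **Inputs (all from the article).** Difference δ = 5; SD σ = 14 at each time; correlation r = 0.8; two-sided α = .05; power 90%; 1:1 allocation.

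**Step 1: SD of change.** With two time points, the group-by-time test is a two-sample t test on change from baseline.

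Var(change) = 2σ²(1 − r) = 2 × 196 × 0.2 = 78.4, so SD = 8.854.

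**Step 2: required number.** By normal approximation:

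n per arm = 2 × (1.960 + 1.2816)² × 78.4 / 25 = 65.9, so 66 per arm, 132 in total.

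With the noncentral t on 2n − 2 degrees of freedom, it is 67 per arm, **134 in total**. The article's own factor gives 134 × 1.1 = 147.4, so about 148 to randomise.

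**Step 3: the more efficient analysis.** Adjusting for baseline gives variance σ²(1 − r²) = 196 × 0.36 = 70.56 (SD 8.4), and 61 per arm, **122 in total**.

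**Step 4: can 88 be recovered?** Totals at δ = 5, normal approximation / noncentral t:

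| Reading | Change score | Baseline-adjusted |
|---|---|---|
| Two-sided, 90% (as stated) | 132 / 134 | 120 / 122 |
| One-sided, 90% | 108 / 110 | 98 / 100 |
| Two-sided, 80% | 100 / 102 | 90 / 92 |
| One-sided, 80% | 78 / 80 | 70 / 72 |

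Other error terms at two-sided 90% are further away: follow-up values alone give 330 / 332, the group main effect over both visits 298 / 300, and an SD of 14√(1 − r) gives 66 / 68. No variant tried at 90% power gives 88.

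**Step 5: what would give 88.** Under the stated model at 90% power, 88 results if one input changes: r about 0.87, or SD about 11.3, or a difference of about 6.2 mmol/mol.

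**Step 6: power at the stated inputs (noncentral t, δ = 5).**

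| Completers | Change score | Baseline-adjusted |
|---|---|---|
| 88 | 74.5% | 78.8% |
| 96 | 78.2% | 82.3% |

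With change scores, the difference detectable at 90% power is 6.2 mmol/mol with 88 completers and 5.9 with 96.

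**Sensitivity.** If r were 0.7 rather than 0.8, Var(change) = 2 × 196 × 0.3 = 117.6 (SD 10.84), and power with 96 completers would be 61%.

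**The case against.** Nobody can reasonably defend 88 at beta .1 with these inputs. The case on the other side concerns what may be concluded from that.

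First, one reading comes close. A baseline-adjusted comparison at 80% two-sided power gives, by normal approximation, 2 × (1.960 + 0.8416)² × 70.56 / 25 = 44.3 per arm, or 88.6 in total. Truncated, that is 88; properly rounded up, it is 90. So the slip may lie in the reported beta. This stands as a possible explanation, but it contradicts the stated beta and the described repeated-measures model, so it does not rescue the paragraph.

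Second, the mismatch does not show which element is wrong. If the correlation or SD was misprinted, 88 could be right and the 90% real. This also stands, and it is why every power figure here is conditional on the stated inputs.

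Third, with baseline adjustment the type II error is 21.2% (88) or 17.7% (96), so the full range is about 18–25%. That is correct, but the planned group-by-time model corresponds to the change score, for which 22–25% is the relevant range. Any gain in precision from the planned covariates cannot be quantified from the article.

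Fourth, the practical harm is limited. Enrolment is complete, confidence intervals will be reported, and neither the estimate nor the type I error is affected. At 96 completers, power for 6 mmol/mol is about 91%. This is a good reason not to ask for more participants. It is not a reason to leave an incorrect power claim in print.

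**Conclusion.** The concern holds. At the stated inputs, the required number of completers is 134 (122 with baseline adjustment), against the 88 reported. Power for 5 mmol/mol is 74.5% with 88 completers and 78.2% with 96, or 78.8% and 82.3% with baseline adjustment. The type II error under the stated model is more than double the declared 10%.

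These figures assume SD 14 at both visits, correlation 0.8, two-sided .05 and equal arms. The 96-completer figures assume no loss at all, although the extra eight are meant partly to cover dropout.

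The figures refer to reaching P<.05 only. The Hypotheses section also requires the observed difference to be at least 5 mmol/mol. If the true difference is exactly 5, that happens only about half the time, so the chance of claiming superiority is lower still.

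**What to change.** Rerun the GLMPOWER program, identify whether an input or the result was misreported, and correct it in the Sample Size Calculation section and the abstract.

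If the inputs prove to be right, replace the claim with wording such as: *At SD 14 and correlation 0.8, power to detect 5 mmol/mol at two-sided .05 is about 75% with 88 completers and 78% if all 96 complete (79% and 82% with baseline adjustment). With change scores, 90% power holds for a difference of about 6 mmol/mol.* The figures should be tied to completers, not to the number randomised.

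If an input was misprinted, give the value used and its source.

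The cost is one paragraph and one line of the abstract, with a less favourable stated power if the inputs stand. The conduct of the trial does not change.

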#### Data Management

Data will be entered directly into electronic case report forms using REDCap, licensed by the Capital Region of Denmark, or saved electronically. All forms are filled out during (or immediately after) each visit. Errors and corrections are logged as provided by the REDCap interface. For CGM, source data will be registered in web-based software (LibreView, Abbott).

#### Statistical Analysis

An intention-to-treat analysis, encompassing all randomized participants, will be conducted upon completion of the last participant’s final visit. A per-protocol analysis will be carried out, including participants who demonstrate compliance throughout the intervention. Data will be presented using standard descriptive statistics, with means and SDs for normally distributed data and medians with IQRs for data not conforming to normal distribution. Changes from baseline and distinctions in delta values between groups will be assessed using linear mixed-effects models, considering the outcome as a function of group, time, and the interaction between group and time, and accounting for a participant-specific random intercept. The adequacy of assumptions regarding normality and homogeneity of variances will be verified through graphical methods, and data will be log-transformed for analysis and subsequently back-transformed for presentation. In cases where model assumptions are not met even after logarithmic transformation, nonparametric statistical tests will be used. Statistically significant findings will be determined with *P*<.05 (2-tailed). To assess the potential impact of missing data on the primary outcome, a sensitivity analysis will be conducted, involving multiple imputations with missing data at follow-up, which will be included in the imputation process with the control group. Results will be presented as estimated mean changes, accompanied by 95% CIs, degrees of freedom, and, if appropriate, the test value.

Covariables such as age, sex, diabetes duration, and so on, will be included in analyses to assess their potential influence on the outcomes. This approach will allow us to adjust for confounding factors and provide an accurate estimation of the intervention's impact. In addition, if the intervention proves effective, a health economic evaluation will be conducted to estimate the cost per person. This evaluation will consider direct costs, for example, staff time and technology, alongside potential cost savings from improved health outcomes, reduced complications, and fewer health care visits.

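### The primary mixed model leaves each arm's baseline mean free, so with complete data it is a change-score analysis carrying about 90% of the information of a baseline-adjusted one

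*Protocol article*

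**What the plan says.** The Primary Outcome section states: "The primary outcome is changes in HbA_1c_ (mmol/mol) from baseline to the end of the 1-year intervention". The Statistical Analysis section gives the method: "Changes from baseline and distinctions in delta values between groups will be assessed using linear mixed-effects models", with the model "considering the outcome as a function of group, time, and the interaction between group and time, and accounting for a participant-specific random intercept". Baseline HbA1c is therefore an outcome value in the model, and nothing ties the two arms to a common baseline mean.

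On covariates the same section says: "Covariables such as age, sex, diabetes duration, and so on, will be included in analyses to assess their potential influence on the outcomes". Baseline HbA1c is not among those named.

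The Hypotheses section bases the superiority claim on a "baseline-corrected difference between the 2 groups". That difference must reach 5 mmol/mol as a point estimate and also have P<.05. The correction is not defined there. The only description the article offers is the difference in deltas in the Statistical Analysis section.

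**The concern.** In a 1:1 randomised trial the expected baseline means are equal. A model that estimates a separate baseline mean for each arm ignores this and subtracts the whole observed baseline difference, whereas only the fraction given by the baseline-to-follow-up correlation is expected to persist. This has two consequences. The treatment contrast has a larger variance than it needs. And, given a chance imbalance at baseline, the estimate is pushed in a predictable direction.

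Both matter more than usual here. The Results section reports that enrolment is complete, so precision can no longer be bought with participants. The superiority rule also compares the point estimate with a fixed cut-off, so a shift of a few tenths of a mmol/mol can decide the claim.

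**Working it through.** **Inputs.** Sample Size Calculation: SD 14 mmol/mol at each time point, correlation r = 0.8, difference 5.0 mmol/mol, α = .05, β = .1, 1:1 allocation, 88 raised to 96. Statistical Analysis: two-tailed test. I take the primary model to use two time points, baseline and 1 year, as the Abstract and the sample size section do, although Table 1 ticks HbA1c at further visits in between.

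**The plan's own figure.** Total N = 2 × 2 × SD² × (1.960 + 1.282)² / 5².
- Change score: 2 × 2 × 78.4 × 10.51 / 25, which rounds up to 66 per arm, 132 in total.
- Baseline-adjusted: 2 × 2 × 70.56 × 10.51 / 25, which rounds up to 60 per arm, 120 in total.

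Neither gives the stated 88. That is a separate problem. It matters here only because power must be recomputed and not read from the protocol.

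**Step 1: what the model estimates.** With both values present for everyone, the group-by-time term is a within-person contrast, so it equals the difference in mean change. Fitting the stated model to one simulated data set with 44 per arm gave an interaction of -3.831 (SE 1.597). The difference in mean change was -3.831 (SE 1.597).

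**Step 2: whether the covariates help.** A covariate that is constant within a participant cancels from the within-person difference. Adding a simulated age covariate as a main effect to another simulated data set left the interaction at -2.8488.

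**Step 3: information.**
- Variance of change: 2 × 14² × (1 - 0.8) = 78.4, SD 8.854.
- Baseline-adjusted variance: 14² × (1 - 0.8²) = 70.56, SD 8.40.
- Ratio: 70.56 / 78.4 = (1 + r)/2 = 0.90. Put the other way, the change-score variance is about 11% larger (78.4 / 70.56 = 1.11).
- In 20,000 simulated trials with 44 per arm the ratio was 0.904.

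**Step 4: precision and power for P<.05 at a true effect of 5 (noncentral t).**

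| | Change score | Baseline-adjusted |
|---|---|---|
| SE, 48 per arm | 8.854 × √(2/48) = 1.807 | 8.40 × √(2/48) = 1.715 |
| Power, 48 per arm | 78.2% | 82.3% |
| Power, 44 per arm | 74.5% | 78.8% |

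In variance terms the gain equals 96 / 0.90 ≈ 107 participants, about 11 more than 96.

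**Step 5: sensitivity to r (assumed values, 48 per arm).** At r = 0.7 the information ratio is 0.85 and power is 60.9% against 67.9%. At r = 0.6 the ratio is 0.80 and power is 49.1% against 58.1%. At r = 0.9 the ratio is 0.95.

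**Step 6: conditional shift.** The standard error of the baseline difference is 14 × √(2/48) = 2.86 mmol/mol. For an imbalance of that size the change-score estimate shifts by (1 - 0.8) × 2.86 = 0.57 mmol/mol. That is 0.57 / 5 = 11% of the cut-off, or about 0.3 of the estimate's own standard error. The shift favours whichever arm starts higher.

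**Step 7: the two-part rule.** At 48 per arm, P<.05 needs an estimate of only about 3.6 (change score) or 3.4 (adjusted), so the 5 mmol/mol cut-off is the binding condition. The chance of claiming superiority is Φ((true effect - 5)/SE):

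| True effect | Change score | Baseline-adjusted |
|---|---|---|
| 4 | 29.0% | 28.0% |
| 5 | 50.0% | 50.0% |
| 6 | 71.0% | 72.0% |
| 7 | 86.6% | 87.8% |

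**The case against.** The strongest reply is that nothing here is wrong. The outcome is defined as change, the analysis compares changes, and the sample size rests on a two-time-point repeated-measures model. The three agree, and the estimator is unbiased over randomisations. That stands: this is a matter of efficiency and of conditional bias, not of validity.

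A second reply is that the gain is small where it counts. A reader might infer from the rise from 78% to 82% that adjustment makes a successful trial more likely by four points. The documents do not support that. Under the two-part rule in the Hypotheses section the gain is nil at a true effect of 5 and about one point at 6 or 7. Nor does adjustment bring power to the stated 90%.

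A third reply is that the open covariate list and the undefined phrase in the Hypotheses section leave room for baseline adjustment. They do not state it, however, and by Step 2 a participant-level main effect would leave the contrast unchanged with complete data.

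A reader might also infer that, under the present model, participants without follow-up contribute nothing. That is not so. In a simulated set of 96 with 19 lacking follow-up, raising by 10 mmol/mol only the baselines of the intervention-arm participants without follow-up moved the interaction from -2.60 to -3.06. The completers' difference in change stayed at -2.60. The identity in Step 1 is exact only with complete data.

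Finally, a common baseline mean presumes equal expected baselines. Randomisation takes place before the first visit, and baseline blood is drawn before visit 1 in an open-label trial, so baseline is apparently sampled after allocation. Because it precedes the visit content, this is probably harmless, but it should be confirmed.

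**Conclusion.** The point holds as a modest and nearly free improvement. As fixed, the primary model uses about 90% of the information available from data already collected, and it leaves the estimate open to a shift of about 0.57 mmol/mol for a chance baseline imbalance of ordinary size. The shift is the more practical concern, because the claim depends on a point-estimate cut-off.

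The figures assume equal SDs of 14, r = 0.8, 48 per arm and complete follow-up. A lower correlation, which selection on HbA1c of at least 53 mmol/mol could produce, would make the loss larger. The finding does not show that the planned analysis is invalid.

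**What to change.** Before group-level outcome data are examined, make the deciding primary model a baseline-constrained mixed model: HbA1c on time and group-by-time, a common baseline mean for the two arms, and an unstructured covariance. It keeps participants without follow-up in the analysis. ANCOVA of 1-year HbA1c on group and baseline HbA1c is an alternative, but it matches the constrained model closely only when follow-up is complete, since ordinary ANCOVA drops those without a 1-year value.

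State that this one model supplies both the estimate and the P value for the superiority rule, define the baseline correction in the Hypotheses section accordingly, and move the other covariates to sensitivity analyses. Confirm that the baseline sample precedes any intervention content. The cost is one model statement and a dated record of the change. No new data are needed.
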